**Genome-wide association study**

The GWAS will be conducted using an Affymetrix Genome-Wide Human SNP Array 6.0, followed by a systematic quality control step before the association analysis.

1. **Inclusion and Exclusion criteria**

**6.1 Inclusion criteria**

1. Histologically confirmed unresectable adenocarcinoma of colorectum
2. ≥ 18 years old
3. measurable disease, defined according to the Response Evaluation Criteria In Solid Tumors version 1.1 (RECIST1.1)
4. Unresectable metastatic disease or first recurrence/metastasis after adjuvant therapy and not suitable for operation
5. Without expected course of radiotherapy during the first-line chemotherapy
6. No previous CPT-11 exposure
7. ECOG performance status (PS) 0-2
8. Not pregnant or nursing
9. Voluntarily signed the informed consent
10. Total bilirubin ≤ 1.5 times upper limit of normal (ULN)
11. AST and ALT ≤ 2.5 times ULN (≤ 5 times ULN if liver metastases present)
12. Creatinine clearance > 50 ml/min or serum creatinine ≤ 1.5 times ULN

**6.2 Exclusion criteria**

1. Brain metastases
2. Severe bone marrow failure and cannot be corrected
3. Chronic diarrhea history
4. Bowel obstruction without control
5. Mental illness without control
6. Clinically significant (i.e., active) cardiovascular disease, including any of the following: Cerebrovascular accidents/Myocardial infarction/Unstable angina/ New York Heart Association class II-IV congestive heart failure/Serious cardiac arrhythmia requiring medication/Uncontrolled hypertension
7. Other co-existing malignancy or malignancy diagnosed within the past 5 years, except for basal cell or squamous cell carcinoma, or carcinoma in situ of the cervix
8. Pelvic radiotherapy in the past 1 year
9. Known allergy to any of the components of the study medications
10. Serious, no healing wound or ulcer

**6.3 Withdrew criteria**

1. Disease progression
2. Intolerable toxicities
3. Patients asked to withdrew from study due to any reason
4. Loss of follow-up
5. Death due to any cause
6. **7. Chemotherapy regimen and dose modifications**

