What’s more, in different populations, genotype variants are more or less frequent. Remarkable interethnic differences in the distributions of UGT1A1 genetic polymorphisms have been known. The allele frequency of UGT1A1*28 among Caucasians is higher (0.3 to 0.4) than that among Asians (0.1 to 0.2). On the contrary, other variant alleles in the coding regions were found only in Asians.[13](#_ENREF_13)

Does Topo1 immunohistochemistry have any effect on the clinical response or prognosis for colorectal cancer patients treated with 5-FU/CPT-11 regimen? It is debated now. Some studies showed that it does not differ in TS or Topo-1 expression level in tumor.[14](#_ENREF_14) But some indicated that patients with moderate/high level of Topo-1 benefited from CPT-11.[15](#_ENREF_15) How about Topo1 gene polymorphism? Hoskins demenstrated that TOP1 and TDP1 htSNPs were related to grade 3/4 neutropenia (P = 0.04) and response (P = 0.04), respectively. [16](#_ENREF_16)But that’s not enough.

For the three limitations mentioned in the preface part, we think it is essential to carry out a prospective study in the relationship between the irinogenetics and CPT-11 toxicity, as well as the effectiveness or clinical outcome in China.

1. **Candidate genes**

- Topo1
- Carboxylesterase (CES)
- CYP3A4 cytochrome P450, family 3, subfamily A, polypeptide 4
- UGT1A1
- [ATP-binding cassette (ABC) transporters](http://en.wikipedia.org/wiki/ATP-binding_cassette_transporter)

1. **Objective and endpoints**

**Objective:** To determine the correlation between irinogenetics and irinotecan -related severe toxicities or tumor response in Chinese mCRC patients.

**Primary endpoints:** The correlation between SNP and ORR. The correlation between SNP and adverse events of Grade ≥3 (blood toxicities, diarrhea and any other serious adverse event).

**Secondary endpoints:** The correlation between SNP and PFS/OS.

1. **Research design**

Patients who meet the inclusion criteria 1-12

Record the clinical message

Collect blood samples after the consent of patients

Evaluation of target lesions

AE/toxicity

eg: diarrhe

neutropenia ect.

OS

PFS

Blood samples of each patient

Genoe-wide association study or relavant candidate gene study

The associations of each polymorphism with tumor response, toxicity, and clinical outcome (survival) will be analyzed.

1. **Method**

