**7.1 Chemotherapy regimen**

FOLFIRI

Irinotecan 180 mg/m2 IV over 30-90 minutes, day 1

Leucovorin 400 mg/ m2 IV infusion to match duration of irinotecan infusion, day 1

5-FU 400 mg/ m2 IV bolus on day 1, then 1200 mg/ m2 /day x 2 days (total 2400 mg/ m2 over 46-48 hours) continuous infusion

Repeat every 2 weeks (14 days are one cycle) until PD or intolerable toxicities.

The starting dose of irinotecan is 180mg/m2 and then it will be reduced lower than 180mg/m2 according to dose modification table.

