**7.2 Dose modifications table 1.**

| Adverse effect | Grade | Dose reduction | | |
| --- | --- | --- | --- | --- |
| First time | Second time | Third time |
| Neutropenia or leukopenia | Ⅳ | Irinotecan reduce to 75%-80% | Irinotecan reduce to 50% | withdraw |
| Febrile neutropenia | Ⅲ |
| Thrombocytopenia and bleeding | Ⅳ | withdraw |  |  |
| Thrombocytopenia without bleeding | Ⅲ-Ⅳ | Irinotecan reduce to 75%-80% | Irinotecan reduce to 50% | withdraw |
| Non-hematologic toxicity (diarrhea, intestinal obstruction etc.) | Ⅳ | withdraw |  |  |
| Ⅲ | Irinotecan reduce to 75%-80% | Irinotecan reduce to 50% | withdraw |
| AST, ALT and serum creatinine meet the exclusion criteria and cannot be corrected in a week |  | withdraw |  |  |
| Bilirubin >1.5 - ≤ 3 times of upper limit of normal（ULN） |  | Irinotecan reduce to 50%-60% | withdraw |  |
| Bilirubin > 3 times of ULN |  | withdraw |  |  |

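### Section 6.3 does not separate stopping chemotherapy from leaving the study; read literally, it ends survival follow-up at progression and tumour assessment at a toxicity stop

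*Protocol*

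**What the plan says.** Section 6.3 of the protocol is a single five-item list of withdrawal criteria. Items 1 and 2 are "Disease progression" and "Intolerable toxicities". Item 3 is "Patients asked to withdrew from study due to any reason". Items 4 and 5 are loss to follow-up and death.

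Section 7.1 gives FOLFIRI in 14-day cycles "until PD or intolerable toxicities", so the same two events already end chemotherapy. The dose table in 7.2 uses the same verb as its last step, for example "Thrombocytopenia and bleeding | Ⅳ | withdraw", without saying whether the patient leaves the drug or the study.

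The section on objective and endpoints makes "The correlation between SNP and ORR" and "The correlation between SNP and adverse events of Grade ≥3" primary and "The correlation between SNP and PFS/OS" secondary. The tumour response section times RECIST 1.1 assessment by each six weeks of chemotherapy. Section 12.2 analyses PFS and OS by Kaplan–Meier and Cox regression, and also names a third time-to-event variable, IR-TTF, without defining it.

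The protocol has no statement on follow-up after withdrawal, in either direction.

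**The concern.** Item 3 is the only item that says what is being left, and it names the study. Loss to follow-up and death can only be exits from the study. Since 7.1 already stops chemotherapy at progression or intolerable toxicity, a site may well take 6.3 to add something: that such patients leave the study.

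Two kinds of data would then go uncollected.

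- **OS.** Deaths after progression would not be recorded. What remained would be deaths without prior progression, with progressed patients censored at the moment their prognosis worsens. That is not overall survival.
- **PFS and, in part, response.** A patient who stops for toxicity before progression would have no further scans. The trial's hypothesis is that genotype predicts toxicity, so these losses would be linked to genotype. Such a link does not by itself bias a Cox comparison between genotypes. It does so if, within a genotype, patients who stop for toxicity progress at a different rate from those who continue, which is plausible because they are no longer on treatment.

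Censoring rules can be left to an SAP. Collection of the data cannot: no SAP recovers deaths or scans that sites were not told to record.

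**Working it through.** No figure in the protocol depends on this point, and the sample sizes in 12.1 are unaffected. The check is a comparison of the text under two readings, then an illustration of size.

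**1. The two readings**

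| Item | Withdrawal = leaving the study | Withdrawal = stopping chemotherapy |
|---|---|---|
| 6.3, items 3 to 5 | Fits | Fits poorly |
| 7.1, same two events end treatment | 6.3 adds a study exit | 6.3 repeats 7.1 |
| 7.2, last step of a dose table | Fits poorly | Fits |
| OS as endpoint; Cox model in 12.2 | Conflicts | Fits |
| Scans timed by chemotherapy | No scans after a toxicity stop | Same gap: no off-treatment schedule |

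Neither reading is excluded. The last row is a gap under both.

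**2. OS under the literal reading**

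Inputs:
- Carrier share: 1 − 0.85² = 0.2775, from the 15% allele frequency in the GWAS part of 12.1, with Hardy–Weinberg proportions and dominant coding (the coding is assumed; the protocol names no inheritance model).
- Deaths with full follow-up: 80 (assumed).
- Share of deaths that follow progression: 80–95% (assumed).

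Deaths still observed: 80 × 0.20 = 16, down to 80 × 0.05 = 4.

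Formula: SE(log HR) = 1/√(D × 0.2775 × 0.7225).

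| Deaths D | SE(log HR) | 95% limits: HR divided and multiplied by exp(1.96 × SE) |
|---|---|---|
| 80 | 0.25 | about 1.6 |
| 16 | 0.56 | about 3.0 |
| 4 | 1.12 | about 9.0 |

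The inflation factor is 1/√(share of deaths still observed): 1/√0.20 = 2.24 and 1/√0.05 = 4.47. It does not depend on the assumed 80 deaths or on the carrier share. With the 20% allele frequency of the candidate-gene part, carriers are 1 − 0.80² = 0.36, and the same formula gives 0.23 rising to 0.52–1.04.

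A second illustration in terms of power, all inputs assumed except 112 patients and 36% carriers: deaths in 80% of patients, hazard ratio 2, two-sided 0.05. Full follow-up gives about 90 deaths and power 0.88. If only 5–30% of deaths are seen, 4 to 27 remain and power is 0.10 to 0.41.

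Under the treatment-stop reading the OS loss is zero, so the range of effect starts at none.

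**3. Response**

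The first scan falls after about three 14-day cycles. In 7.2 some rows, such as Grade IV non-haematological toxicity, lead to withdrawal at first occurrence and could do so before that scan. The stepwise rows mostly reach it at the third occurrence, which is unlikely so early.

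Take a carrier ORR of 30% (the response rate in 12.1) and assume 10% of carriers leave before a scan:
- left out, and none would have responded: 0.30/0.90 = 33%;
- left out, and they would have responded like the rest: 30%, no bias.

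Counting them as non-responders has its own effect. Assume 112 patients, 36% carriers, a true ORR of 30% in both groups, and early exit in 5–30% of carriers and 2–10% of non-carriers. At the low end the rates become 0.30 × 0.95 = 0.285 and 0.30 × 0.98 = 0.294, an odds ratio of 0.96. At the high end they become 0.21 and 0.27, an odds ratio of 0.72. The true value is 1.00.

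**The case against.** The strongest reply is that 6.3 probably means stopping treatment. The reference to the study attaches to item 3 only. The same two events end chemotherapy in 7.1, and 7.2 uses the verb as the end of a dose-reduction ladder. OS is a named endpoint with a planned analysis, which makes little sense if follow-up stops at progression. The 6.3 list also resembles a set of treatment-failure events, and 12.2 names IR-TTF separately from PFS and OS, although without a definition this is only supportive.

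Much of this stands. A reader might infer that OS does end at progression, or that toxicity-prone genotypes do drop out of the response and PFS data. The protocol states neither. Leaving at progression does no harm to PFS, since progression is the event, and removes no response already recorded. The toxicity that triggers the exit is still captured for the primary toxicity endpoint.

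A reader might also infer that ORR would be inflated in the high-toxicity genotype. That needs two premises the protocol does not supply: that early leavers are left out of the denominator, and that they would not have responded. The denominator is ordinary SAP content.

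The reply does not remove the ambiguity. No section says that follow-up continues after treatment stops, no off-treatment scan schedule exists, and six hospitals (sponsor plus five collaborators) could apply the list differently.

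**Conclusion.** The point holds as a conflict to be reconciled. Section 6.3 mixes treatment stops with study exits, and its literal reading is incompatible with the OS endpoint and with complete PFS data after a toxicity stop. The effect on OS runs from none, under the treatment-stop reading, to a standard error 2.24 to 4.47 times larger under the literal reading. The latter rests on the assumed 80–95% of deaths after progression, and the absolute values 0.25 to 0.56–1.12 also on the assumed 80 deaths and on 28% carriers. The loss of PFS and response data is confined to patients who stop for toxicity before progression or before a first scan. Its size cannot be derived from the protocol, and no direction of bias in ORR is established.

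This should be fixed, but it does not rank with the gravest faults: OS and PFS are secondary, and the reading that does no damage to OS is well supported. It still merits action because data not collected cannot be recovered.

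**What to change.** Reconcile 6.3 with the endpoints section, 7.1, 7.2, the tumour response section and 12.2 by splitting it in two:

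- **Discontinuation of study chemotherapy:** progression and intolerable toxicity. This does not end study participation.
- **Withdrawal from the study:** withdrawn consent and loss to follow-up. Death is recorded as an endpoint event.

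State that after chemotherapy stops, tumour assessment continues until progression and survival follow-up continues until death or data cut-off. Give the scan schedule in calendar time so that it applies off treatment. Say in 7.2 which sense of withdrawal the table uses.

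No rule on the ORR denominator is needed here. Counting a missing scan as non-response is debatable, can itself create a genotype association, and belongs in the SAP.

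The cost is a short amendment, some follow-up contacts, and routine scans after treatment in patients who stopped for toxicity. No dose or treatment-stopping rule changes.

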**7.1 Chemotherapy regimen**

FOLFIRI

Irinotecan 180 mg/m2 IV over 30-90 minutes, day 1

Leucovorin 400 mg/ m2 IV infusion to match duration of irinotecan infusion, day 1

5-FU 400 mg/ m2 IV bolus on day 1, then 1200 mg/ m2 /day x 2 days (total 2400 mg/ m2 over 46-48 hours) continuous infusion

Repeat every 2 weeks (14 days are one cycle) until PD or intolerable toxicities.

The starting dose of irinotecan is 180mg/m2 and then it will be reduced lower than 180mg/m2 according to dose modification table.

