**GWAS study**

We set statistical limits for the type I error α = 0.01, 1-β = 0.8, two-sided test, provided the target SNP frequency in the population > 15%, and OR> 4, according to the known lowest FOLFIRI first-line treatment induced severe adverse reactions (about 20%) and treatment efficacy (about 30%), we calculate that the needed samples will be 112 by software Quanto (Version 1.2.4), 1:1 ratio.

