12.2 Statistical method

Hardy-Weinberg equilibrium will be assessed. The χ2 test will be used to compare the observed genotype frequencies with those expected under Hardy-Weinberg equilibrium.

The associations of each polymorphism with tumor response, toxicity, and demographic variables were examined using contingency tables and the Fisher’s exact test. Multivariate Logistic Regression will be performed to ascertain which genotype independently predicted response or toxicity. Odds ratios (OR) and their 95% confidence interval (CI) were calculated as estimates of the correlations. Kaplan–Meier estimates the PFS and OS. To evaluate the relationship between genotypes and PFS, IR-TTF, and OS, multivariate Cox regression (forward LR) performed, adjusting for potential confounding covariates. Hazard ratios (HR) and their 95% CI were calculated as estimates of the correlations. A value of *p* < 0.05 was considered statistically significant in a two-tailed test.

Statistical analyses were performed using SPSS16.0 (SPSS Inc, Chicago, IL) and two-sided P-value of 0.05 is considered significant.

1. **Research institutions**

Sponsor

- Tongji Hospital, Tongji Medical College, Science and Technology of Huazhong University

Collaborators

- Union Hospital, Tongji Medical College, Science and Technology of Huazhong University
- Zhongnan Hospital, Wuhan University
- Wuhan 8th Hospital, Wuhan, People’s Republic of China
- Wuhan Pu-Ai Hospital, Tongji Medical College, Huazhong University of Science and Technology
- Hubei Cancer Hospital

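### Grade ≥3 toxicity is tested as yes/no with no stated window while treatment runs until progression, so a SNP that only delays progression can appear as a toxicity marker

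*Protocol*

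**What the plan says.** Under Objective and endpoints, the second primary endpoint is "The correlation between SNP and adverse events of Grade ≥3 (blood toxicities, diarrhea and any other serious adverse event"). No time frame, cycle limit or exposure denominator is attached to it.

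Section 7.1 sets the length of treatment: "Repeat every 2 weeks (14 days are one cycle) until PD or intolerable toxicities". Section 6.3 lists "Disease progression" first among the withdrawal criteria. Tumour response is assessed every 6 weeks, which is every three 14-day cycles.

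Section 12.2 fixes the toxicity analysis: "The associations of each polymorphism with tumor response, toxicity, and demographic variables were examined using contingency tables and the Fisher’s exact test". It adds: "Multivariate Logistic Regression will be performed to ascertain which genotype independently predicted response or toxicity". No term for cycles, cumulative dose or time on treatment is named. Time-to-event modelling is kept for other outcomes: "To evaluate the relationship between genotypes and PFS, IR-TTF, and OS, multivariate Cox regression (forward LR) performed".

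**The concern.** A patient who progresses at the first scan has had about three cycles in which to have a Grade ≥3 event. A patient whose disease stays controlled has no upper limit. A yes/no count over treatment therefore mixes two things: how toxic each cycle is, and how many cycles were given.

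This matters more here than in a study of toxicity alone. The same SNPs are tested against response (co-primary) and against PFS and OS (secondary). A genotype that truly delays progression lengthens its carriers' time at risk, and Fisher's test and the logistic model as described have no means of separating that from a higher toxicity rate. At stake is whether a SNP reported as predicting irinotecan toxicity does so, or only marks patients who stayed on treatment longer.

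**Working it through.** **Inputs from the protocol.** The GWAS paragraph of 12.1 gives "type I error α = 0.01, 1-β = 0.8, two-sided test", SNP frequency 15%, OR 4, severe adverse reactions about 20%, and 112 samples at 1:1. The background gives Grade 3-4 neutropenia of about 50%, used here as an upper toxicity rate. Section 12.2 declares significance at p<0.05.

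**Inputs that are assumptions.** The protocol gives no PFS and no timing of toxicity. The effect of a SNP on progression is taken as HR 0.80, 0.67 or 0.50, and median PFS as 6-10 months.

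**Step 1: the plan's own figure.** With a dominant model and Hardy-Weinberg proportions, carriers make up 1 − 0.85² = 27.75%. OR 4 with 20% overall toxicity gives 13.2% in non-carriers and 37.8% in carriers. Carrier frequency is then 0.2775 × 0.378/0.20 ≈ 52.4% in cases and 0.2775 × 0.622/0.80 ≈ 21.6% in controls. The two-proportion formula (two-sided α 0.01, power 80%, 1:1) gives 56 per group, 112 in total, as stated. The candidate-gene inputs give 2 × 43 = 86, also as stated. The present point does not alter these figures; N = 112 and 27.75% carriers are carried forward.

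**Step 2: constant toxicity hazard, no true SNP effect on toxicity.** Let λ be the hazard of a first Grade ≥3 event and μ the hazard of progression, which ends treatment.

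- Non-carriers: P(event on treatment) = λ/(λ+μ), so the odds are λ/μ.
- Carriers, progression hazard HR × μ: the odds are λ/(HR × μ).
- Spurious OR = 1/HR, whatever the base rate or median PFS.

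| HR for progression | Spurious OR | Carriers, if 20% in non-carriers | Carriers, if 50% in non-carriers |
|---|---|---|---|
| 0.80 | 1.25 | 23.8% | 55.6% |
| 0.67 | 1.49 | 27.2% | 59.9% |
| 0.50 | 2.00 | 33.3% | 66.7% |

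Example: 20% is odds of 0.25; 0.25/0.50 = 0.50; 0.50/1.50 = 33.3%.

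**Step 3: how often it would be declared significant.** Simulated Fisher's exact test, N = 112, 27.75% carriers, p<0.05, 4,000 runs:

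| HR for progression | Rejection, base 20% | Rejection, base 50% |
|---|---|---|
| 1.00 | 3.9% | 4.3% |
| 0.67 | 10.7% | 13.1% |
| 0.50 | 27.9% | 32.5% |

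**Step 4: sensitivity to timing** (median PFS 6-10 months, base rates 20% and 50%).

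| Toxicity pattern | HR 0.80 | HR 0.67 | HR 0.50 |
|---|---|---|---|
| Constant hazard | 1.25 | 1.49 | 2.00 |
| Hazard falls to one quarter after 2 months | 1.17-1.19 | 1.33-1.38 | 1.66-1.77 |

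If all toxicity falls within the first 2 months, the OR is 1.02-1.10 across the three HRs and rejection stays close to the no-effect level.

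**Step 5: what a common window does.** With constant hazard and median PFS 8 months, P(event by t) = λ/(λ+μ) × (1 − exp(−(λ+μ)t)). Over 12 weeks the spurious OR is 1.02-1.07; over 6 weeks it is 1.01-1.03. The price is events. With an assumed 3% risk per cycle, 1 − 0.97³ = 8.7% have an event by cycle 3, against 1 − 0.97⁶ = 16.7% by cycle 6 and 1 − 0.97¹² = 30.6% by cycle 12. The loss is 1 − 8.7/16.7 = 48% to 1 − 8.7/30.6, about 71%.

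**Illustration only.** At 3% per cycle, exactly 6 versus exactly 12 cycles gives OR (0.306/0.694)/(0.167/0.833) = 2.2. At 2-5% per cycle the OR is 2.1-2.4, and 3.3-3.7 for 4 versus 12 cycles. These figures need every patient of one genotype to stop at the same cycle, so they show the mechanism and not a likely size.

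**The case against.** The strongest reply is that whole-course counting is an inference. No sentence in the protocol says Grade ≥3 events are counted until treatment ends, Fisher's test and logistic regression are compatible with a fixed window, and a statistical analysis plan could set one. That stands, and it makes the finding conditional. It does not remove it: the protocol itself pairs open-ended treatment with a binary test and keeps Cox regression for PFS, IR-TTF and OS.

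Second, the bias is bounded. It lies well below the design ORs of 3.5 and 4, it needs a SNP with a real effect on progression, and it nearly vanishes if toxicity comes early. For UGT1A1, the background reports a strong association with neutropenia and diarrhoea but none with response or survival, so for that gene the confounding path may be absent. All of this stands and limits the size.

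Three stronger readings are tempting, and the documents do not support them:

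- *A progression-only SNP will be taken for a toxicity marker.* Even at HR 0.50 with constant hazard, about two thirds or more of trials of 112 would not reach p<0.05.
- *The study cannot answer its toxicity question.* A bias that ranges from nearly nil to an OR of 2.00, and that an analysis of the same data can correct, does not justify that.
- *The count mixes full-dose and reduced-dose exposure.* A yes/no outcome is settled by the first Grade ≥3 event. Apart from the bilirubin row, the irinotecan reductions in the table in 7.2 follow Grade III-IV events, which already count. Mixing could matter mainly if event types are analysed separately.

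**Conclusion.** The point holds in conditional form. If Grade ≥3 events are counted over the whole treatment course, the toxicity OR is confounded with disease control, and a SNP acting only on progression can appear as a toxicity marker. The inflation reaches 1/HR under constant hazard, 1.25 to 2.00 over HR 0.80 to 0.50. At HR 0.67 to 0.50 the false-positive rate rises from about 4% to 11-32% at N = 112. It is smaller with front-loaded risk and close to nil with purely early toxicity. The size rests on assumed progression HRs, PFS and toxicity timing, none of which the protocol supplies; the direction does not depend on the assumed values. The stated sample sizes are unaffected. This is worth correcting because section 12.2 names a binary method where a better one is already in use for other endpoints.

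**What to change.** In section 12.2, add an analysis of time, in cycles, from dose 1 to first Grade ≥3 event, censored at the end of treatment, using the Cox model already planned for PFS and OS. Report the cause-specific hazard ratio for each SNP. Require the association to appear there before a SNP is called a toxicity marker; a SNP significant only in the yes/no table should be described as possibly reflecting longer treatment. State in the endpoint definition the period over which events are counted.

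Add a common early window, for example to the end of cycle 3, as a sensitivity analysis. It should not become the primary endpoint: it removes nearly all of the bias but, at 3% per cycle, would discard about half or more of the events and leave 8.7%, well under the 20% used for sizing.

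The cost is a little more analysis and a few sentences of text. Beyond the cycle of each first Grade ≥3 event and the last cycle given, nothing is needed, so no new data collection should be required.
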